## 48 1.2 Introduction of a wash out phase

49 In addition to the specifications made in the study protocol (version 1.07 of 18.05.2016)  
 50 regarding randomization and inclusion of patients in the intervention and control groups, a  
 51 one-month wash-out phase will be introduced between the end of the intervention phase  
 52 (after the inclusion of 15 patients in one institution) and the start of the control phase (before  
 53 the inclusion of 15 additional patients in the institution who are educated but do not receive a  
 54 consil). This phase is intended to ensure that knowledge of improved treatment strategies  
 55 gained during the intervention phase approaches pre-study routines, allowing clearer  
 56 differentiation between outcomes the intervention and control phases. Accordingly, no wash  
 57 out phase is required between the end of the control phase and a subsequent intervention  
 58 phase.

59

60

61

---

62 [name].med. **[name]**, Head of the study Date

63

64

65

---

66 **[name]**, M.D., Deputy Study Director Date

67

68

69

70 *[name].med. **[name]**, Biometrician*

Date

71

## 1.1 Extension of the Secondary Endpoints

In addition to the procedure of following up patients after 30 and 90 days as defined in the study protocol version 1.09 dated 25/07/2016 under 1.4., 3.2., 4.6, 7.1, 7.6, it is planned to capture the long-term survival of patients by follow-up telephone calls also 18 months after the diagnosis of *S.aureus* bacteremia. The data to be collected correspond to those of the 30- and 90-day follow-up (successful contact, new hospitalization and, if applicable, reason for admission, death of the patient, new clinical complaints).

The patient information was modified accordingly. For the patients included so far, consent is requested on the phone and documented accordingly. If no verbal consent is given, the patient will be censored at 18 months. The evaluation of long-term survival is performed separately and is not part of the primary evaluation.

---

*[name].med. [name]*, Head of the study

Date

---

*Priv.Do. Dr.med. [name]*, Deputy Head of the Study

Date

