## 385 7.7 Follow-up surveys

386 The survival of the patients and the recurrence rate will be recorded up to 90 days after  
387 diagnosis of SAB. For this purpose, the patients or, if they are not available, the primary care  
388 physician or the study centers will be interviewed by telephone 30 and 90 days after  
389 diagnosis. Patient visits are not planned.

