## 392 7.9 End of study participation

393 The regular study end date for each study participant is 90 days after diagnosis of SAB.

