## 705 10.6 Privacy

706 As part of the study, it is necessary to collect and process personal data from the study  
707 participants (e.g., full name, initials of first and last name, date of birth, address) and data on  
708 treatment and the course of the disease (e.g., medical findings, types of treatment,  
709 prescribed medication). These data are collected at the study centers and stored  
710 electronically in pseudonymized form (i.e., without direct reference to the patient's name)  
711 using a patient identification number. The data will then be extracted at the centers by the  
712 SUPPORT study nurse and entered into the CRF, transmitted to the study center, reviewed  
713 and analyzed. In the event of withdrawal of consent to the study by the patient, including  
714 further data collection, no further data will be collected from the date of withdrawal. The data  
715 collected so far will continue to be used and evaluated within the study. If a patient only  
716 discontinues the study treatment, the data required for the study can continue to be collected  
717 and used.

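### The 18-month amendment's censoring rule for already-enrolled patients without verbal consent, read as written, counts unobserved time as event-free and overstates long-term survival

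*Protocol*

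**What the plan says.** The relevant text is section 1.1, Extension of the Secondary Endpoints, of the amendment appended to the protocol. It adds a contact beyond day 90: "it is planned to capture the long-term survival of patients by follow-up telephone calls also 18 months after the diagnosis of" *S. aureus* bacteremia. The items to collect match those of the 30- and 90-day contacts and include death. New patients receive revised patient information. For earlier patients, "For the patients included so far, consent is requested on the phone and documented accordingly". The rule at issue follows directly: "If no verbal consent is given, the patient will be censored at 18 months". The section then limits the role of the endpoint: "The evaluation of long-term survival is performed separately and is not part of the primary evaluation".

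Follow-up in the body of the protocol stops at day 90. Section 7.7 states: "The survival of the patients and the recurrence rate will be recorded up to 90 days after" diagnosis. Section 7.9 states: "The regular study end date for each study participant is 90 days after diagnosis of SAB". Section 7.7 also names fallback informants (the primary care physician or the study centers) for patients who cannot be reached.

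**The concern.** A censoring time should be the last time a patient was known to be event-free. A patient enrolled before the amendment who does not agree to the extension was, as a rule, last observed at the day-90 contact. Censoring at 18 months keeps that patient in the risk set for a further period in which nobody looked for a death, so any death in that period is lost.

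There is also a selective element. A patient who died after day 90 and before the consent call gives no verbal consent. The sentence makes no exception for this case, so taken literally it turns that death into event-free time to 18 months. Being without consent then depends partly on the outcome.

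The rule also sits poorly beside section 10.6. For full withdrawal of consent, that section says that "further data collection, no further data will be collected from the date of withdrawal" and that data gathered up to then remain in use. Declining the extension is not the same as withdrawing, but crediting time that was never observed runs against the same principle.

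At stake is the estimate of 18-month survival, which is the endpoint this amendment exists to add. The sentence is the only censoring rule that the document states for it.

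**Working it through.** The protocol gives no figure on this point, so there is none to reproduce. The check is on what the rule does to the estimate.

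**Inputs from the protocol**
- Last scheduled contact without the extension: day 90 (7.7, 7.9).
- Censoring time under the rule: 18 months, about 548 days (amendment, 1.1).
- Unobserved time credited: 548 − 90 = 458 days, about 15 months.

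**Inputs that must be assumed**
- S90, survival to day 90: 0.65 to 0.75.
- m, risk of death between day 90 and 18 months in day-90 survivors: 0.10 to 0.30.
- q, share of day-90 survivors without verbal consent: 0.10 to 0.50.

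**Formulas, with non-consent unrelated to prognosis**
- True 18-month survival: S90 × (1 − m). Censoring non-consenters at day 90 estimates the same quantity.
- Rule as written: S90 × (1 − (1 − q) × m), because only deaths among consenters are seen.
- Overstatement: S90 × q × m.

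| S90 | m | q | True | As written | Overstatement |
|---|---|---|---|---|---|
| 0.65 | 0.10 | 0.10 | 0.585 | 0.5915 | 0.0065 |
| 0.65 | 0.20 | 0.30 | 0.520 | 0.559 | 0.039 |
| 0.75 | 0.20 | 0.30 | 0.600 | 0.645 | 0.045 |
| 0.75 | 0.30 | 0.50 | 0.525 | 0.6375 | 0.1125 |

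The first and last rows are the extremes of the assumed ranges.

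**Kaplan-Meier check.** A simulation of 20,000 patients used S90 = 0.70, m = 0.20 and q = 0.30. By formula the truth is 0.70 × 0.80 = 0.560, and the rule gives 0.70 × 0.86 = 0.602. The simulated values were 0.556 for the truth, 0.556 when non-consenters were censored at day 90, and 0.598 when they were censored at 18 months. The rule is therefore about 4 points too high.

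**Deaths before the consent call.** If a fraction d of the deaths after day 90 falls among patients without consent, d replaces q and the overstatement is S90 × d × m. Here censoring at the last contact is not a full cure, because lack of consent is caused by the death. The death has to be counted where it can be established.

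**Whole cohort.** These figures apply to patients enrolled before the amendment. For all patients, multiply by the share already enrolled when the amendment took effect, which the document does not state.

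**Group comparison.** With the same q in both groups and independence from prognosis, post-day-90 mortality is multiplied by (1 − q) in each. The absolute difference shrinks by that factor. The risk ratio, (1 − q)m₁ / (1 − q)m₀ = m₁ / m₀, does not change.

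**A check on the remedy.** Suppose known deaths among non-consenters are counted while living refusers are censored at day 90. Take 100 day-90 survivors, 25 deaths all ascertained, and 15 refusers who are in fact alive throughout. Estimated mortality is then about 25/85 = 29% instead of 25/100 = 25%. The refusal call is itself evidence of being alive, and the censoring date has to use it.

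**The case against.** The strongest reply is that the sentence is a loose, translated statement meaning only that such a patient has no 18-month observation. It names no survival model. On that reading nothing is credited, and the exact censoring date could be set in an analysis plan that is not at hand. This reading is possible, but the text does not say so: it gives a time point for censoring, and an analyst who follows it gets the bias shown above.

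A second reply is that the timing of the consent call is not stated. If patients are asked at the 18-month call, one who answers and declines is known to be alive then, and censoring there is right. If they are asked at a day-30 or day-90 call, no death can fall between day 90 and the request. Both points stand. The lost deaths concern only patients who had passed day 90 and died before being asked, and the document gives no count of them.

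Third, death is among the items to be collected at 18 months, and section 7.7 already provides other informants. So deaths are evidently meant to be captured, and the sentence may be aimed only at people who were asked and said no. That is a fair reading of intent. The amendment does not, however, say whether those informants may be used for someone who never agreed to the extension.

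A reader might infer that deaths recorded by day 90 are also overwritten. In the simulation above, applying the rule to 30% of all patients regardless of earlier death gave 0.689 against 0.556. The documents do not support this inference, because those deaths were collected under the consent given at enrolment and nothing in the amendment sets them aside. A reader might equally infer that the comparison between groups is diluted on every scale. With equal, independent non-consent only the absolute difference shrinks.

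**Conclusion.** The concern holds in a limited form. The amendment states a censoring rule that, followed literally, overstates 18-month survival among patients enrolled before it. The size is S90 × q × m: about 0.65 to 11 percentage points over the assumed ranges, and about 4 points in the central case. These numbers rest wholly on assumed survival and non-consent rates. The formula also assumes that non-consent is unrelated to prognosis, except where deaths before the call are treated separately.

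A reader might infer that the trial's main result is at risk. It is not: the long-term evaluation is separate, and the 30-day primary endpoint, the 90-day endpoints and the sample size are untouched. Severity is moderate. The wording should be corrected because it is the only stated censoring rule for this endpoint and, as written, gives a wrong estimate.

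**What to change.** Replace the sentence in section 1.1 of the amendment with:

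> Patients without consent to the 18-month contact are censored at the date they were last known to be alive, including the date of the consent call if they were reached and declined. Patients found to have died before they could be asked are not treated as refusals: where permitted, their vital status is obtained from the sources in section 7.7 and the death is counted at its date. Where vital status cannot be obtained, they are censored at the last contact.

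Report, per group, the number of patients censored for lack of consent and the number not reached.

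The cost is a short text change and slightly less person-time at risk. Design, sample size and the primary analysis do not change. Some informative censoring will remain where deaths before the consent call cannot be ascertained, and the per-group counts let a reader judge how much.
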